**Fig. 5 Fig5:**
[figure not shown]
**a** Placement of probes, **b** Image of example data trace. X-axis: time. Y-axis: local muscle oxygen saturation in percent. 1: Baseline values are recorded for 120 sec. 2: 2 minutes extension exercise. 3: Resting 10 seconds. 4: 2 minutes extension, 5: Recovery phase and hyperaemia (The images are original pictures taken by the team)

After 2 minutes with recording of the baseline value, the subject shall perform a neck muscle fatigue test, i.e. the participants shall extend isometrically the neck from neutral position against a submaximal load. If the participant feels fatigued but latest after 2 minutes, a resting period of 10 seconds is implemented and monitoring continued. The procedure shall be repeated one more time afterwards. After the second extension task, a 2 minutes resting period will be recorded (Fig. 5b).

### Questionnaires

Questionnaires will be used to assess factors related to cervical spine history, neck pain, prior aviator experience and physical activity (Supplementary Material 2). They will be applied electronically with an iPad (Apple Inc., USA) and/or in paper.

### DXA protocol

The measurement of the cervical spine will be performed on a standard DXA machine using the lateral spine setting. The DXA scan will start at the level of T1 and will continue until C1 (Fig. 6). For DXA devices without C-arm, the subject shall be placed in lateral position; for devices with C-arm, the subject shall be placed in supine position with the cervical spine in one line with the thoracic spine to avoid rotation artifacts. A stable foam pillow shall be put under the head to get the cervical spine parallel to the table. Both shoulders will be drawn as far as possible forward (in lateral position only) and downward to prevent a superimposition of the shoulder with the cervical spine. The subject shall be instructed to remain still during scanning (as scans might need to be repeated).

**Fig. 6 Fig6:**
[figure not shown]
Example image of DXA cervical spine scan with regions of interest traced. Note that “1”, “2”, “3”, “4” refer, respectively to C3, C4, C5 and C6

The evaluation will be performed manually with creation of custom (instead of “standard”) ROIs individually for the vertebral bodies C3 to C6 for the respective subject. Subject and vertebrae specific ROIs will be saved as an individual ROI template and used for evaluation of follow-up measurements to ensure reproducibility.

### Blinding and bias control

To reduce the risk of bias, we will assign random codes to each measurement timepoint for each participant in the study. Thus, the individual performing the data analysis will not be aware of the individual participants. Also, the EMG measurement order will be randomized and instructions to the participants will be standardized to reduce the risk of bias.

### Statistical analysis

We will use the R software (× 64 v4.0.2) for statistical analysis. A repeated measures ANOVA design and testing for within-factor (i.e. pre-flight vs. post-flight) is planned for each parameter. If assumptions of normality of distribution of residuals are not held (as assessed via quantile-quantile plots), then non-parametric methods for longitudinal data [43] will be implemented. Where some data is missing, a maximum likelihood based approach will be used [44]. Due to the large number of statistical comparisons to be performed as part of hypothesis testing, the false discovery rate method will be used to reduce the risk of type I statistical error. We will use a significance level of *p* < 0.05.

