**Methods:**

A cohort study with astronauts will be conducted. The data collection will involve four main components: a) Magnetic resonance imaging (MRI); b) cervical 3D kinematics; c) an Integrated Protocol consisting of maximal and submaximal voluntary contractions of the neck muscles, endurance testing of the neck muscles, neck muscle fatigue testing and questionnaires; and d) dual energy X-ray absorptiometry (DXA) examination. Measurements will be conducted at several time points before and after astronauts visit the International Space Station. The main outcomes of interest are adaptations in the cervical discs, muscles and bones.

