## Methods

This cohort study will include astronauts who have stayed at the International Space Station (ISS) in order to identify the factors involved in spinal dysfunction and cervical IVD herniation. We will not include pregnant women, subjects that have non-MRI compatible metal implants, or electronic implants. It will be conducted as a multi-center study at the Johnson Space Center, Houston (Texas); European Astronaut Centre, Cologne (Germany) and the University of Texas Medical Branch, Houston (Texas). The planned protocol is in accordance with the Helsinki Declaration of ethical principles [24] and approved by the NASA (Study000000222, NASA MPA Number NASA7116301606HR) and ESA (ILSRA-2014-0033) Institutional Review Board. This study was prospectively registered in the German Clinical Trials Register (Approved on 08 October 2021, registration number DRKS00026777). The STROBE checklist (Supplementary material 1) was used to report the components for this study protocol [25].

The planned investigation will be presented to the crew members by the science team members ([name], GA) in an Informed Consent Briefing (ICB) of the NASA Human Research Program. Additionally, a video ICB illustrating all required science and operational aspects of the study will be prepared. After the ICB, the crew members have 3–4 weeks to express their interest in participating in the presented study. A written informed consent will be obtained from the participants.

The number of astronauts a research group can recruit for measurements is always limited. Using data from an earlier study [23], we calculated test-retest repeatability of average cervical disc volume (average of all discs from C2/3 to C7/T1) with 1.5 years between testing sessions. We observed a correlation of 0.964 (95% CI: 0.913–0.986) between measures on the same 21 participants separated by 1.5 years. The mean (SD) average cervical disc volume was 2.01(0.31) cm^3^. If 10 astronauts are to be measured, pre- and post-flight, and given the above repeatability data, the calculated detectable effect size would be a 2.07% difference (95%CI: 1.31–3.24%) in average cervical disc volume before and after spaceflight. This assumed a repeated measures ANOVA design and testing for within-factor (i.e. pre-flight vs. post-flight) differences with an alpha-level of 0.05 and a power of 0.80. These calculations were performed in G*Power3 version 3.1.2 [26, 27].

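### The normality check uses residuals that a two-level pre/post ANOVA makes symmetric by construction, so it hides skewed changes and weakens the trigger for the non-parametric method

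*Protocol article*

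**What the plan says.** The Statistical analysis section of the protocol article names one model for all outcomes: "A repeated measures ANOVA design and testing for within-factor (i.e. pre-flight vs. post-flight) is planned for each parameter". The next sentence sets the rule for leaving it: "If assumptions of normality of distribution of residuals are not held (as assessed via quantile-quantile plots), then non-parametric methods for longitudinal data" are to be used. It does not say which residuals are meant, and it does not mention looking at the pre/post changes. Missing values are handled separately: "Where some data is missing, a maximum likelihood based approach will be used".

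The sample-size paragraph in Methods rests on the same comparison. It starts from "If 10 astronauts are to be measured, pre- and post-flight" and assumes "testing for within-factor (i.e. pre-flight vs. post-flight) differences".

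One statement pulls the other way. The abstract announces more than two sessions: "Measurements will be conducted at several time points before and after astronauts visit the International Space Station". The article does not say whether these enter the ANOVA as separate levels or reduce to one pre-flight and one post-flight value.

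**The concern.** The F test for a two-level within-subject factor is the square of the paired t test. What matters for it is the distribution of the within-person changes, one per astronaut. Pooling the model's residuals replaces those 10 changes by 10 centred half-changes together with their 10 mirror images. Skewness cancels exactly, although skewness is the departure that a Q-Q plot would most usefully reveal here.

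This plot chooses between the ANOVA and the non-parametric method for every parameter. If a few astronauts respond strongly, or if an outcome changes multiplicatively, the changes can be skewed. The ANOVA would then often be kept where the rule means to abandon it, and the greater power of a rank method on such data would be lost.

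**Working it through.** **Inputs.** From the Methods sample-size paragraph: n = 10, correlation 0.964 between repeat measures, mean disc volume 2.01 cm³ with SD 0.31, alpha 0.05, power 0.80, stated detectable difference 2.07%. From Statistical analysis: a pre/post factor and a Q-Q plot of residuals. The article gives no distribution for the changes, so the skewed shapes below are assumptions.

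**Step 1: the plan's own figure.** For a within-factor with m = 2 levels, the noncentrality is λ = f²·n·m/(1−ρ), with an F(1, 9) test. Power 0.80 needs f = 0.1336, so λ = 0.1336² × 20 / 0.036 ≈ 9.92. Then f × SD / mean = 0.1336 × 0.31 / 2.01 = 2.06%, against the stated 2.07%. The sizing model is therefore the two-level one. (This quantity is half the pre/post difference, which is a separate matter.)

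**Step 2: the residuals.** Write r_ij = y_ij − ȳ_i. − ȳ_.j + ȳ.. with j = 1 (pre) and 2 (post), and d_i = y_i2 − y_i1. With two levels, y_i2 − ȳ_i. = d_i/2 and ȳ_.2 − ȳ.. = d̄/2. Hence

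r_i2 = (d_i − d̄)/2 and r_i1 = −(d_i − d̄)/2.

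In simulation the skewness of the 20 residuals was zero to machine precision in every data set. The 10 changes had mean sample skewness 0.96 (exponential) and 1.25 (log-normal, σ = 1).

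**Step 3: how often non-normality is flagged.** Two numeric stand-ins for reading the plot: the Q-Q correlation with a simulated 5% cutoff (20,000 data sets) and Shapiro-Wilk at 5% (5,000 data sets).

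| Assumed changes | Q-Q corr., 10 changes | Q-Q corr., 20 residuals | Shapiro-Wilk, changes | Shapiro-Wilk, residuals |
|---|---|---|---|---|
| Normal | 5.0% | 5.0% | 5.0% | 3.3% |
| Exponential | 41.7% | 21.7% | 43.5% | 13.9% |
| Log-normal, σ = 1 | 59.0% | 35.6% | 61.6% | 25.6% |
| Log-normal, σ = 0.5 | 24.6% | 14.4% | 24.2% | 8.9% |
| Chi-square, 4 df | 23.7% | 13.3% | 23.9% | 8.5% |

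The Q-Q residual column uses a cutoff calibrated to mirrored residuals. The ratio of residual to change flag rates runs from 13.9/43.5 = 0.32 to 35.6/59.0 = 0.60.

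**Step 4: what the weaker trigger costs.** Shapiro-Wilk was the trigger and the Wilcoxon signed-rank test stood in for the cited rank method.

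- Power, residual-triggered against change-triggered: 48% to 58% (multiplicative skewed change), 40% to 46% (shifted log-normal), 58% to 64% (shifted exponential). When pre and post are exchangeable, error stayed at about 5% or below.
- Type I error when skewed changes have mean zero: 9.8% to 9.6% (exponential) and 15.6% to 15.2% (log-normal, σ = 1; a second run gave 15.0% to 14.4%). Always using the t test gave 10.0% and 15.4%.

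**The case against.** **Two levels are not certain.** The abstract speaks of several sessions before and after flight, and the pre/post wording may describe the contrast rather than the number of levels. With independent exponential errors, mean residual skewness was 0.48 with three levels and 0.77 with four, so the exact mirror property is then lost. This stands as a limit on the point. It does not remove it: pre versus post is the only factor written down, and the sizing uses it. More sessions also do not guarantee that skew becomes visible. In one example with one pre and two post values, the second post change being half the first, mean residual skewness was again about zero.

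**The type of residual is not named.** Marginal residuals are not mirrored, and likelihood-based ones only approximately. This also stands. However, marginal residuals mix in the spread between astronauts and do not isolate the changes, and random-intercept conditional residuals, at about the protocol's SD and correlation, had mean skewness of only 0.06.

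**A condensed article may leave diagnostics to a fuller plan.** That would answer an omission. Here the article itself fixes the object inspected, the tool and the consequence.

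**The error rate barely changes.** This is right. For skewed changes with mean zero, the excess over 5% comes from skewness at n=10, not from which quantity is plotted. A reader might infer that checking the changes would restore nominal error or coverage; Step 4 does not support that. Nor would a sign-flip permutation test be a way round: it too assumes symmetric differences, and it rejected 9.4% (exponential) and 14.8% (log-normal) in the same setting.

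**Nothing shows that the changes are skewed.** True. The only outcome with data is disc volume, and its summary figures say nothing about skew in the changes.

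**Conclusion.** For the pre/post comparison as written, with one value per period and complete data, the symmetry is exact algebra: a Q-Q plot of within-subject residuals cannot show skewness of the changes. The switch then triggers at roughly one third to three fifths of the rate available from the same 10 changes. The consequence is mainly lost power for skewed outcomes, 6 to 10 percentage points in the scenarios tried; type I error for a zero mean change is almost unaffected.

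A reader might infer that the check can never detect skewed data and that the switch will not fire. The figures do not support that: skewed changes still appear as heavy symmetric tails and were flagged in 8.5% to 35.6% of data sets.

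The sizes rest on assumed change distributions and effect sizes, on numeric stand-ins for a judgement by eye, and on Wilcoxon in place of the cited rank method. The exact result also needs a two-level analysis and within-subject residuals, neither of which the article settles fully. The change is worth making because it costs almost nothing.

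**What to change.** In the Statistical analysis section, state that for the pre/post contrast the Q-Q plot is drawn on the within-person post-minus-pre differences, one per astronaut, in place of the pooled model residuals. Add that if more than two sessions enter the model, the check is made on the person-level contrast being tested.

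The cost is one or two sentences and no new data. A few more parameters will move to the rank method. At n=10 the check remains of limited sensitivity: even on the changes, the Q-Q correlation flagged only about 24% to 59% of the skewed data sets above. The amendment should therefore not claim that it secures the nominal error rate or coverage.

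### The 80% power is for disc volume tested alone at 0.05, but the planned analysis puts it under a false discovery rate correction with no exemption, so its power is lower

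*Protocol article*

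**What the plan says.** The only power statement is in the Methods of the protocol article. It concerns average cervical disc volume over C2/3 to C7/T1: "If 10 astronauts are to be measured, pre- and post-flight", with the repeatability figures from an earlier study, "the calculated detectable effect size would be a 2.07% difference (95%CI: 1.31–3.24%) in average cervical disc volume before and after spaceflight". The design is a repeated measures ANOVA with a within-subject pre/post factor, "with an alpha-level of 0.05 and a power of 0.80".

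The Statistical analysis section uses the same kind of test throughout: "testing for within-factor (i.e. pre-flight vs. post-flight) is planned for each parameter". It then adds: "Due to the large number of statistical comparisons to be performed as part of hypothesis testing, the false discovery rate method will be used". The significance level is 0.05. The section does not name the procedure, the number of tests or the family, and it sets no parameter apart. The abstract describes the main outcomes only as changes in discs, muscles and bones. The Background lists 18 hypotheses.

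**The concern.** The power calculation and the decision rule use different alphas. Disc volume was powered as if it were the only test. As written, it is one of many tests sharing a correction, so the 80% does not describe the test that will be run.

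Astronauts are scarce, and the article says recruitment is always limited, so lost power cannot easily be bought back with more participants. Disc volume heads the list of hypotheses, and the last two (stress and strain, herniation risk) build on it. A non-significant result could be read as a negative finding from a study with 80% power when the actual power was well below that.

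**Working it through.** **Inputs, all from the sample-size paragraph.** n = 10. "We observed a correlation of 0.964 (95% CI: 0.913–0.986"). "The mean (SD) average cervical disc volume was 2.01(0.31") cm³. Alpha 0.05, power 0.80, two sessions.

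**1. Reproduce the article's figure.** For a within-factor test with two sessions, the noncentrality is λ = f² × n × 2/(1 − r) on 1 and 9 degrees of freedom. Solving for 80% power gives f = 0.1336. Then f × SD/mean = 0.1336 × 0.31/2.01 = 2.06%, against the stated 2.07%. The stated limits of 1.31% and 3.24% come out at 1.29% and 3.20%.

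**2. Convert to a pre/post difference.** With two levels, f is half the standardised difference between them, so the difference with 80% power is 2 × 2.06% = 4.12%. A paired t test gives the same answer:

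- SD of the difference = 0.31 × √(2 × (1 − 0.964)) = 0.0832 cm³
- required standardised difference dz = 0.996
- 0.996 × 0.0832/2.01 = 4.12%

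The 2.07% is therefore labelled as a difference but is half of one. That is a separate matter. The steps below start from dz = 0.996, which has 80% power unadjusted by construction, so the loss shown is due to the correction alone.

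**3. Threshold under the correction.** Benjamini–Hochberg at 5% with m tests, of which k are rejected, uses the threshold 0.05 × k/m. This is at most 0.05 and equals 0.05 only when k = m. In any family of two or more, power for disc volume is below 80% unless all the other tests are certain to be rejected.

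**4. Power by simulation.** Assumptions: n = 10, independent tests, every true effect at dz = 0.996.

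| Tests in family | Only disc volume truly changes | All truly change |
|---|---|---|
| 3 | about 61% | about 77% |
| 5 | about 51% | about 76% |
| 16 | about 31% | about 76% |

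Sixteen is 18 hypotheses less the last two, which are not direct pre/post comparisons in astronauts, with one test each. Intermediate values for 16 tests are about 45% with 4 true effects, 60% with 8 and 68% with 12. With a correlation of 0.5 between parameters the figures are similar or slightly lower: 31% with one true effect and 72% with all 16.

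**5. Detectable difference at the strictest step.** For 16 tests the lowest threshold is 0.05/16 = 0.003125. Power at dz = 0.996 is then 30%, and the difference detectable with 80% power rises from 4.12% to 6.6%.

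**The case against.** The strongest reply is that the article never claims 80% power after correction. It gives a detectable effect for one variable in a cohort study whose size is set by astronaut availability. The family may also be defined in an analysis plan that is not shown. Families by domain (discs, muscles, bones) would fit the text as well as a single one. This stands as a limit on the size of the loss: a single study-wide family is an inference, and 31% is the low end for 16 tests, not a property of the plan. It does not remove the mismatch, because even a family of 3 gives only 61–77%.

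Three stronger readings are tempting and should not be made.

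- A reader might count every EMG variable, task and muscle and arrive at a family of about 200. The article lists what will be calculated, but ties the correction to comparisons made for hypothesis testing. A family of that size is conjecture.
- A reader might infer that each extra EMG variable lowers the chance of detecting a disc change. That is true of variables that do not change. Variables that do change can raise it: 16 tests with one true effect give about 31%, whereas 50 tests with 25 true effects give about 55–58%.
- The abstract says "Measurements will be conducted at several time points before and after astronauts visit the International Space Station", while the analysis names only a pre/post factor. A reader might infer that the sessions are pooled and a recovering change diluted. Nothing in the text says that sessions are averaged. The schedule is in Fig. 1, which is not available here, so no dilution figure can be supported.

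**Conclusion.** The point holds. The stated 80% power belongs to an unadjusted test of average cervical disc volume, and the planned decision rule does not deliver it. The article itself states both the power basis and the correction, so this is not merely a detail left to another document.

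For the effect with 80% unadjusted power, the planned power is about 61–77% with 3 tests, 51–76% with 5 and 31–76% with 16. No simulated case reached 80%. The direction follows from the procedure. The size rests on assumptions that the article does not settle: that the method is Benjamini–Hochberg at 5%, the family size, the share and size of true effects, and the dependence between parameters.

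**What to change.** Do one of the following before the data are analysed.

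1. Name average cervical disc volume (C2/3 to C7/T1), pre- versus post-flight, as the single primary test at two-sided 0.05, outside the correction. Apply the false discovery rate method to all other parameters. The alpha in the sample-size paragraph then matches the test. The small downside is that the other outcomes become secondary.
2. Keep all parameters on an equal footing, but state the procedure and the family, and restate the detectable difference in the sample-size paragraph under that rule. This keeps the structure and reports a larger detectable difference, for example up to 6.6% if the family has 16 tests.

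Either is a change of wording and needs no new data or measurements. In both cases the percentage quoted should be the full pre/post difference.

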### Further data analysis, 3D modelling, laboratory testing

Using the data obtained from testing with the astronaut collective, the following laboratory examinations will be performed:

Cervical IVDs will be loaded in a dynamic disc-loading simulator [45] to provoke IVD herniation and lesions. Three groups of specimens and the parameters adjusted pending outcomes from the astronaut testing: (i) normal discs, (ii) hyperhydrated discs after storing the disc-segments in hypo-osmotic fluid (lower osmolarity), and (iii) hypohydrated discs after storing the disc-segments in hyper-osmotic fluid (high osmolarity). A load combination with flexion, lateral bending right, axial rotation right, and axial compression can reproducibly create a posterior or postero-lateral herniation. The herniations and lesions will be investigated with Ultra-High Field 11.7 Tesla MRI [46].FEM studies: calculations of stresses and strains with the IVD in different hydration states and complex motions will be performed.

## Discussion

The results of this study will have broader implications for understanding intervertebral disc herniation risk in the cervical spine in the wider population on Earth. At a later stage, this will also help in developing proper countermeasures to minimize the risk of developing such conditions in astronauts. In case the drop-out rate is higher than expected, the project will take more time since the number of astronauts is limited.

The data from this project will also be used as an input for ground-based in-vitro studies with cadaver spines in a custom-built dynamic disc loading simulator to provoke disc herniations in normal and hydrated discs. Additionally, it will be used as an input to ground-based finite element modelling to estimate stress and strains in discs at different locations during motion, both for normal and hyperhydrated discs.

This includes several different investigations on the cervical spine to capture a range of possible influencing factors. The potential limitations of the current project is the lack of a non-astronaut ground-based control collected. This would help to control for the effect of normal aging in the findings. In our original peer-reviewed research proposal, we planned a 2:1 ratio for time-synchronous ground-based controls to astronauts, but we have not yet secured funding to support this. The generalisability of the findings will be limited to astronauts.

